#### Feasibility

Feasibility will be analysed through evaluation of eligibility, recruitment and retention (in line with CONSORT extension recommendations). Adherence to intervention will also be assessed. Completeness of outcome measures will be reported, and 80% would be considered appropriate for each measure. Feasibility will be determined and estimates of effect size and outcome variability will be calculated to inform future planned studies.

#### Eligibility

Eligibility will be assessed through screening logs. We will report on the proportion of screened participants who were deemed eligible for the study, and summarise the reasons for ineligibility.

#### Recruitment

Recruitment will be evaluated based on the final number of participants who were successfully consented and randomised.

#### Retention (i.e. assessments)

Retention will be measured by evaluating the proportion of participants who were lost to follow-up.

#### Adherence

Successful adherence to the intervention will be defined as at least 75% of the participants having completed cocoa consumption [33]. We will assess discontinuation of the intervention. Further aspects of adherence will be measured by the percentage of fatigue texts completed by participants and those who wore the accelerometer-axivity watches. If the proportion is less than this but greater than 65%, we will consider adjusting the intervention to increase this in future investigations. An adherence rate lower than this would require substantial changes to the intervention and therefore require further piloting.

#### Acceptability

The acceptability of the intervention will be measured through the end-of-study interview, which uses questions to measure the extent to which participants found the intervention and materials useful, enjoyable and beneficial.

Exploratory analyses will be used to investigate the impact of individual demographic factors as well as theoretical mediators on the short-term benefit of the intervention, using appropriate correlation coefficients.

A generalised linear model analysis will investigate whether fatigue differed between the treatment arms. This will be extended to joint modelling of both fatigue and physical functioning if there is a significant difference in the reported fatigue. Data may be transformed to improve model fit, or different regression approaches used (e.g. negative binomial or Poisson regression).

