### Outcomes

The primary aim of this study is to assess feasibility of the dietary intervention in terms of adherence, safety and process. This will be achieved through the documentation of adherence and any adverse events (AEs), as well as any health-related changes such as gastrointestinal disturbances that may occur during the intervention period. Duration of participation and dropout from the intervention will also be recorded. In order to assess benefits, a range of outcomes will be obtained. Outcome measures includeLevels of physical activity: wearable activity monitors (worn like a watch) [18] and the Physical Activity Scale for the Elderly (PASE) questionnaire [19]Dietary patterns assessed by a nutritionist: three 24-h dietary records [20]Fatigue levels: FSS, Neuro-QOL [21], and during the intervention, a Numerical Rating Scale (NRS) scored from 1 to 10, three times daily which classifies no fatigue as a 1 and very fatigued as a 10.Fatigability: performance on 6-min walk test (physical) [22] and the Adult Memory and Information Processing Battery (AMIBP; mental) [23]Blood markers of inflammation: TNF-alpha, reduced glutathione, a marker of antioxidant status and lipid peroxidationHealth descriptives: EQ5D5L [24] and the Preference-Based Multiple Sclerosis Index (PBMSI) [25], basic health questionnaire, Barthel ADL Index (BI) [26] and Hospital Anxiety and Depression Scale (HADS) [27]

Demographic factors and background factors will be assessed at baseline: medication, age, gender, level of education, type of MS, duration of disease, height, weight and leg length will be assessed at baseline. Participants will be stratified for gender and whether they are on first-line disease-modifying treatments or not.

Table 1 summarises the questionnaires that will be administered throughout the trial and at which visits these measures will be collected.

**Table 1 Tab1:** Outcome measures

Domain to be measured	Outcome measure(s)	Time required	When
Measures of overall health and questionnaires			
1. Health questionnaire and health assessment	General medicine use/health problems, etc.	10 min	1
2. Global fatigue	Neuro quality of life	5 min	1, 2, 3
3. Limitations in daily activity	Barthel Activities in Daily Living Index	5 min	1
4. Quality of life measure	EuroQOL 5D5L and Problem Based Multiple Sclerosis Index	5 min	1, 2, 3
5. Dietary recall	Monitor diet patterns	10 min	1, 2, 3
6. Consent	Verbal followed by written	10 min	1

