### Fatigue

Fatigue will be measured at baseline using the FSS. If participant scores a 4 or above and thus fulfils the criteria to take part in the trial, he or she will then wait 3 days before beginning the intervention. On the fourth day, the participant will begin consuming the coca drink. Directly after the consumption of the drink, participants will rate on an NRS their level of fatigue. This will be followed by two additional measures recorded at 3 p.m. and 8 p.m., daily for the 6 weeks. They will be asked to reply to the text message with a score of fatigue from 1 to 10, 1 being no fatigue and 10 being very fatigued. Smart phones will be provided to those who do not have them and collected after the trial termination, and ease and acceptability of phone use will be documented. Walking endurance will be measured a total of two times (baseline and assessment 3) using a 6-min walk test [22], and sensors will be worn to measure gait during the walk. Gait measurements will be collected via an inertial measurement unit (IMU) [28, 29] attached to the lower spine (lumbar 4 region) by double-sided adhesive tape. Participants are instructed to walk over a 14-m walkway free of obstacles at their self-selected walking speed. Walking speed will be derived from IMU data by using well-established validated algorithms [28, 29].

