### Diet

A total of three 24-h dietary recalls will be administered to provide information about the diet of each participant and to determine any changes that may take place throughout the study. This method is less burdensome for patients than a 7-day food record diary yet will still provide an overall pattern in dietary behaviour throughout the study. Total energy intake is a potential confounder of the study and will therefore be corrected for in the analysis. We advise participants not to change their habitual diet and exercise regimes during the trial.

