### Randomisation

After recruitment, confirmation of eligibility, giving consent and collection of baseline data, patients will be registered and then randomised into one of the two groups, either the control or the test cocoa group. Participants recruited to the study will be randomly allocated the next available study number by the blinded assessor, with 20 participants in each group. The unblinded researcher will randomise participants into the control or intervention group using a computer-generated randomisation groups stratified for gender and DMTs.

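### The fatigue comparison names neither baseline fatigue nor the randomisation strata; followed as written, it is less precise if baseline and follow-up fatigue correlate above about 0.2 to 0.3

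*Protocol article*

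**What the plan says.** **The model.** Under Acceptability, within Statistical methods: "A generalised linear model analysis will investigate whether fatigue differed between the treatment arms". The sentence names no covariate, fatigue scale or time point. The same paragraph does go into other modelling detail: transformation, negative binomial or Poisson alternatives, and a joint model with physical functioning if fatigue differs significantly.

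**The design factors.** Randomisation is carried out "using a computer-generated randomisation groups stratified for gender and DMTs". The Outcomes section agrees: "Participants will be stratified for gender and whether they are on first-line disease-modifying treatments or not".

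**Pre-treatment fatigue.** Table 1 lists Neuro-QOL at all three visits: "2. Global fatigue Neuro quality of life 5 min 1, 2, 3". The FSS is also taken before treatment ("Fatigue will be measured at baseline using the FSS"), and Table 1 lists it at visit 1 only. The daily NRS has no pre-drink value: "Directly after the consumption of the drink, participants will rate on an NRS their level of fatigue".

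**The one correction promised.** Under Diet: "Total energy intake is a potential confounder of the study and will therefore be corrected for in the analysis". The dietary recalls take place at all three visits.

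**Other use of baseline variables.** Statistical methods and Acceptability examine demographic factors and theoretical mediators (the former gives disease or fatigue severity as the example) by correlation coefficients. These analyses are separate from the comparison of arms.

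**The concern.** The quantitative outputs for fatigue are an effect estimate, its 95% confidence interval and a measure of variability. The Objectives, Feasibility and Discussion sections say these will inform a phase III trial, including its sample size.

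The article commits to a between-arm model and to one correction. That correction is for a variable partly measured after randomisation. The Risk management section mentions reports of reduced appetite after dark cocoa, so the drink could itself affect intake. Two sets of variables fixed before treatment, baseline fatigue and the stratification factors, are collected but not named in the model.

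If the sentence is followed as it stands:

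- Variance that baseline fatigue could explain stays in the error term.
- Any chance difference in baseline fatigue between two groups of 20 passes into the estimated effect, in proportion to the baseline to follow-up correlation.
- The SD that comes out of the model is the raw SD, while a baseline-adjusted phase III analysis would be sized on the residual SD.

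**Working it through.** **The plan's own figure.** The sample size of 40 rests on recruitment: 3 × 0.5 = 1.5 patients per week, and 1.5 × 52 = 78 over 12 months, which exceeds 40. No power, SD or effect size is given, so there is no precision calculation to reproduce.

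**Inputs.** From the document: 20 per arm, 95% intervals, two stratification factors. Assumed, because the document does not give them: a continuous outcome analysed by a linear model, a baseline to follow-up correlation ρ between 0 and 0.7, and strata with no prognostic value. Results are in units of the outcome SD.

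**Step 1: half-width with arm as the only term.**

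t(0.975, 38) × √(2/20) = 2.024 × 0.316 = 0.640.

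**Step 2: half-width with baseline fatigue, gender and DMT use added.** The residual degrees of freedom are 38 − 3 = 35. Stratified allocation balances gender and DMT use almost exactly, so only chance imbalance in baseline fatigue costs precision. This is an average variance factor of about 35/34:

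t(0.975, 35) × √[(2/20) × (1 − ρ²) × 35/34], with t = 2.030.

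The last column is a simulation with allocation stratified by gender and DMT use, 6,000 trials per row.

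| ρ | Arm only, formula | Adjusted, formula | Arm only / adjusted, simulated |
|---|---|---|---|
| 0 | 0.640 | 0.651 | 0.635 / 0.648 |
| 0.2 | 0.640 | 0.638 | 0.636 / 0.636 |
| 0.3 | 0.640 | 0.621 | 0.637 / 0.618 |
| 0.5 | 0.640 | 0.564 | 0.636 / 0.561 |
| 0.7 | 0.640 | 0.465 | 0.635 / 0.463 |

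The formula gives an interval 0.651/0.640 − 1 = about 2% wider at ρ = 0, about 12% narrower at 0.5 (0.564/0.640 = 0.88) and about 27% narrower at 0.7 (0.465/0.640 = 0.73).

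**Step 3: break-even.** Setting the two formulas equal gives ρ ≈ 0.18. If gender and DMT use were balanced only by chance, the factor 35/34 becomes 37/34. The half-widths are then 0.580 at ρ = 0.5 and 0.478 at 0.7, break-even is 0.29, and the interval at ρ = 0 is 4.6% wider. With 16 per arm (the article's 80% completeness level), that less favourable break-even is 0.33. Hence the statement of about 0.2 to 0.3.

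**Step 4: chance imbalance.** The baseline difference between arms has standard deviation √(2/20) = 0.32 SD. At ρ = 0.5, an imbalance of that size moves the unadjusted estimate by 0.5 × 0.32 = 0.16 SD. This is the lost precision of Steps 1 and 2 seen within a single trial. It is not an additional loss, and it is not a bias on average.

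**Step 5: variability for phase III.** The residual SD is √(1 − ρ²) of the raw SD: 0.95, 0.87 and 0.71 at ρ = 0.3, 0.5 and 0.7. As an illustration (assumed difference 0.5 SD, two-sided 5%, 90% power), sizing on the raw SD gives 85 per arm. Sizing on the residual SD gives 77, 64 and 43 at those correlations.

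**The case against.** **The text is silent and does not exclude anything.** This is the strongest objection, and much of it stands. A reader might infer that the protocol prescribes an arm-only model, but no sentence says so. A condensed article may leave the covariate list to a full protocol or SAP that is not shown. If the energy-intake correction applies to the fatigue model, that model is already not arm-only, and the comparator in Step 1 is a simplification. The point survives because the article does more than stay silent: it fixes a model, promises one specific correction and sends baseline severity to separate correlations. Within what it commits to, it chose a weaker covariate over better ones already in hand.

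**The gain is not certain.** This stands. It depends on a correlation that the documents do not give. The FSS entry threshold may narrow the range of baseline fatigue and lower that correlation. For the NRS, the correlation would be between two different scales. The figures do not carry over directly to a Poisson or negative binomial model. Prognostic strata would raise the gain, but nothing in the documents shows by how much.

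**Power.** A reader might infer that the trial is underpowered as a result. The primary outcome measures are feasibility and acceptability, and no power target is stated, so interval width is the relevant measure.

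**Phase III size.** A reader might infer that phase III will be wrongly sized. Using the raw SD errs on the conservative side. Baseline and follow-up Neuro-QOL are both collected, so the residual SD can be recovered later.

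**Other outcomes.** It is tempting to extend the point to the walk test, HADS, blood markers and the rest. The article states no separate between-arm model for them, so there is no sentence to amend.

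**Conclusion.** The point holds in limited form. The fatigue model as stated commits to neither baseline fatigue nor the two stratification factors, while the only named correction is for a partly post-randomisation variable. With 20 per arm, a continuous outcome and non-prognostic strata, adjustment would reduce the 95% CI half-width from about 0.64 SD to about 0.56 SD at an assumed correlation of 0.5, and to about 0.46 SD at 0.7. Near 0.2 there is no gain, and at 0 there is a loss of about 2%. The documents do not support saying that covariates are ruled out or that precision will certainly be lost. This is a worthwhile improvement to a secondary analysis and does not threaten the trial's feasibility conclusions.

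**What to change.** In the Acceptability paragraph that states the model:

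1. For Neuro-QOL fatigue, include arm, baseline Neuro-QOL fatigue, gender and DMT use (yes/no).
2. For the daily NRS, use baseline Neuro-QOL fatigue or baseline FSS as the baseline covariate, with the same two stratification factors.
3. Report the adjusted difference with its 95% CI, and give the residual SD and the baseline to follow-up correlation beside the raw SD, so that phase III planners can use whichever matches their analysis.

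The cost is wording only, since every covariate is already collected. The statistical downside is three degrees of freedom (38 to 35), with no gain in precision if the correlation proves low.

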This study sets out to determine the potential benefit and feasibility of implementing a flavonoid dietary intervention that was co-designed with pwMS. We propose that a single drink of flavonoid-rich cocoa taken each morning over a 6-week period will be feasible and acceptable for pwMS. We will also estimate the variation and change in fatigue to allow for a power calculation to be made for a larger trial. In addition, there is a process evaluation of both quantitative and qualitative components. The study uses a randomised, parallel group controlled design where participants will either be supplied with cocoa rich in flavonoids or a low-flavonoid cocoa drink that looks and tastes the same.

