### Sample size

A sample size of 40 pwMS was deemed appropriate to address feasibility and determine variability of outcome measures [30–32] for a follow-on trial based on a 12-month recruitment period. Approximately five potentially eligible patients with recently diagnosed RRMS attend the clinic at the hospital per week, of which three will potentially fit the inclusion criteria of the study. Considering a recruitment rate of approximately 1.5 patients per week (50%), this would enable a minimum sample of 40 pwMS. The sample size of ≥ 30 also allows for assumptions from the central limit theorem in relation to representation within this group of RRMS with fatigue and should be easily recruitable within the timeframe.

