### Statistical methods

We will report summary statistics for demographics and outcome data of the study participants. The assessment of mediators is important to be able to identify the processes by which the intervention may bring about change. The proportion of adherence to the intervention will be reported descriptively with 95% confidence intervals. Graphical illustration will be used to check distributions of outcome data. As an exploratory trial, the primary outcome measures will be feasibility and acceptability. Results will be presented using point estimates, 95% confidence intervals and *p* values. The primary statistical analysis will be on an intention-to-treat basis, and the primary analysis will use the complete case data set. Exploratory analyses will be used to investigate the impact of individual demographic factors as well as theoretical mediators (i.e. disease/fatigue severity) on the intervention effect using appropriate correlation coefficients.

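### The joint model of fatigue and physical functioning is fitted only if the fatigue difference is significant, in a trial not sized for that test, so the link between the two outcomes may go unreported (minor)

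*Protocol article*

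**What the plan says.** All quotes are from the protocol article.

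- **The model and its condition (Acceptability).** "A generalised linear model analysis will investigate whether fatigue differed between the treatment arms". The next sentence adds: "This will be extended to joint modelling of both fatigue and physical functioning if there is a significant difference in the reported fatigue". The fatigue measure and time point for this test are not named there.
- **Size of the trial.** Sample size: "A sample size of 40 pwMS was deemed appropriate to address feasibility and determine variability of outcome measures". No effect size, SD, significance level or power is given. Randomisation fixes 1:1 allocation "with 20 participants in each group".
- **Purpose.** Statistical methods: "As an exploratory trial, the primary outcome measures will be feasibility and acceptability". Feasibility, under Statistical methods: "estimates of effect size and outcome variability will be calculated to inform future planned studies". Background: "We will also estimate the variation and change in fatigue to allow for a power calculation to be made for a larger trial". The Objectives, the Trial design section and the Feasibility part of the Discussion say the same in substance, the last naming sample size for a phase III trial.
- **Reporting.** Statistical methods: "Results will be presented using point estimates, 95% confidence intervals" and p values, with a complete-case primary analysis.

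Nothing in the article says that the joint model will be reported if the fatigue difference is not significant.

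**The concern.** The condition treats a p value as permission to look at the second outcome. That makes sense in a confirmatory hierarchy, where it protects an error rate. This trial makes no confirmatory efficacy claim, so there is no error rate to protect. What a joint model offers the next trial is how strongly fatigue and physical functioning vary together, and both arm differences set out side by side. That is informative whether or not the fatigue difference passes 5%. The link also belongs to the trial's rationale, since the Discussion part of the Abstract proposes that the drink improves mobility and functioning by acting on fatigue.

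Two things are at stake. The joint information may not be produced. If functioning effects from this model are read only when fatigue is significant, they come from a selected set of results and lean away from zero.

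**Working it through.** **Inputs.** From the article: 20 per arm (Randomisation), complete-case analysis (Statistical methods), and 80% completeness regarded as appropriate for each measure (Feasibility), which gives 0.80 × 20 = 16 per arm as a sensitivity case. Assumed: two-sided 5%, inferred from the 95% confidence intervals; an unadjusted two-sample t-test; and a range of true standardised differences d, because the article gives none. There is no power figure in the plan to reproduce.

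**Step 1. Chance that the joint model is run.** With n per arm, df = 2n − 2 and noncentrality d√(n/2). For n = 20, df = 38 and the critical t is 2.024. At d = 0.5 the noncentrality is 0.5 × √10 = 1.58 and the power is 0.338.

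| True d | 20 per arm | 16 per arm |
|---|---|---|
| 0.2 | 9.5% | 8.5% |
| 0.3 | 15% | 13% |
| 0.4 | 23% | 20% |
| 0.5 | 34% | 28% |
| 0.6 | 46% | 38% |
| 0.8 | 69% | 59% |
| 1.0 | 87% | 78% |

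With 20 per arm the chance reaches 50% at d ≈ 0.64 and 80% at d ≈ 0.91. An observed difference must exceed about 2.024 × √(2/20) = 0.64 SD to be significant.

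**Step 2. Sensitivity to baseline adjustment.** If a baseline measure correlates r with the outcome, the residual SD is multiplied by √(1 − r²). With 20 per arm (normal approximation):

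- d = 0.5: 45% at r = 0.5 and 60% at r = 0.7.
- d = 0.8: 83% at r = 0.5 and 94% at r = 0.7.

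The article does not state such an adjustment. Table 1 lists the FSS at the first visit only, and the Fatigue section starts the numerical ratings after the first drink. Of the named fatigue scales, only Neuro-QOL has a baseline on the same footing as follow-up.

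**Step 3. Inflation of functioning effects read only when the gate opens.** In simulation with 20 per arm, the mean absolute fatigue difference among significant results, in true SD units, is 2.01 times the truth at d = 0.4 and 1.67 times at d = 0.5. If both outcomes have the same true d and the within-arm correlation is ρ, the selection passes to functioning in proportion to ρ. The ratio is about 1 + ρ × (fatigue ratio − 1).

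- d = 0.4: 1 + 0.3 × 1.01 = 1.30, and 1 + 0.5 × 1.01 = 1.51.
- d = 0.5: 1 + 0.3 × 0.67 = 1.20, and 1 + 0.5 × 0.67 = 1.34.

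Direct simulation of both outcomes (200,000 trials per case) gives 1.30, 1.50, 1.20 and 1.33.

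**Step 4. The ungated fatigue estimate.** In the same simulation, the standardised fatigue difference averaged over all trials is about 1.02 times the truth at d = 0.4 and 0.5. The small excess comes from dividing by an estimated SD, not from the gate.

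**The case against.** The strongest reply is that the gate covers little. The fatigue model runs unconditionally, and the Objectives, Background, Statistical methods and Feasibility sections promise effect sizes, intervals and variability with no condition attached. For two continuous outcomes with the same covariates and complete data on both, a bivariate linear model returns the same arm differences as two separate models. What it mainly adds is the correlation, and no section says that phase III sizing depends on it. This stands, and it sets the size of the point.

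It also rules out three stronger readings that a reader might infer.

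- **That the planning information is never produced.** The separate estimates and SDs are promised whatever the p value.
- **That a phase III trial would be undersized on fatigue effects exaggerated about twofold.** Those ratios describe fatigue estimates discarded unless significant, and the protocol does not discard them. The estimate it reports is essentially unbiased (step 4).
- **That the trial has no power for the test.** It was not powered for it, which is different. The chance is 69% at d = 0.8, and baseline adjustment or averaging the repeated fatigue ratings could raise the chances.

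The reply does not supply a reason for the condition. The joint step is still withheld on a criterion unrelated to its purpose.

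**Conclusion.** The point holds in a limited form. The protocol makes the joint model depend on a test for which the trial was not sized, and this conflicts with its estimation aim. With 20 per arm and an unadjusted two-sided 5% test, the model is skipped more often than not for any true d below about 0.64. That is conditional on an effect size the article does not give. With a baseline correlation of 0.7 it no longer holds at d = 0.5, where the chance of running the model is 60%.

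The loss is the joint information, chiefly the fatigue–functioning correlation. Inflation of 1.2 to 1.5 times applies to functioning effects reported only when the gate opens. It assumes true d of 0.4 to 0.5, equal for both outcomes, and a within-arm correlation of 0.3 to 0.5. It would matter only if those effects took the place of the ungated summaries, which no section says. Feasibility, adherence and safety results are unaffected. The importance is minor.

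**What to change.** Delete the significance condition from the sentence on joint modelling. Fit the joint model of fatigue and physical functioning whatever the fatigue p value. Report both arm differences with 95% confidence intervals, both SDs and the correlation between the outcomes, labelled as descriptive inputs to phase III.

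The joint model is then reported in every case, and selection on significance no longer affects the functioning estimates. Keeping the condition at 80% power would instead need about 63 per arm at d = 0.5 or 175 at d = 0.3 (normal approximation), which is out of scale for a feasibility trial. The cost is one clause and a little more analysis work, with no new data.

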8. Speed of information processing	The Adult Memory and Information Processing Battery	5 min	1, 2, 3
9. Depression	Hospital Anxiety and Depression Scale	5 min	1, 2, 3
10. Physical activity	Physical Activity Survey for the Elderly	10 min	1
11. Fatigue	Fatigue Severity Scale	5 min	1
Measures of activity and fatigue			
11. 6-min walk	Fatigue	6 min	1, 3
12. Accelerometer	Activity	2 weeks and 3 days throughout intervention	–
13. Numerical Rating Scale for fatigue	Fatigue	3 times daily for 6 weeks	–
Measures of plasma markers			
14. Venous blood samples	Inflammation, oxidative stress, antioxidant capacity of plasma	5 min	1, 2, 3

1 = baseline assessment; 2 = assessment 2 (3 weeks); 3 = assessment 3 (6 weeks)

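### Poisson regression is offered as an option for fatigue scores that are bounded ratings, not counts, so if it were used its standard error would follow the scale's numbering rather than the spread between participants

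*Protocol article*

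**What the plan says.** Under Statistical methods, Acceptability, the protocol article states: "A generalised linear model analysis will investigate whether fatigue differed between the treatment arms". The same paragraph makes a significant fatigue difference the trigger for a joint model of fatigue and physical functioning, and then adds "Data may be transformed to improve model fit, or different regression approaches used (e.g. negative binomial or Poisson regression". It names no family or link for the starting model, no fatigue measure and no unit of analysis.

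The measures are listed under Outcomes: "Fatigue levels: FSS, Neuro-QOL [21], and during the intervention, a Numerical Rating Scale (NRS) scored from 1 to 10, three times daily". Table 1 gives the NRS as "3 times daily for 6 weeks", Neuro-QOL at all three visits and the FSS at baseline only. The Fatigue section says the first daily rating follows the drink, and continues: "This will be followed by two additional measures recorded at 3 p.m. and 8 p.m., daily for the 6 weeks".

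Randomisation is 1:1, "with 20 participants in each group". Under Statistical methods, "Results will be presented using point estimates, 95% confidence intervals" and p values are promised, and feasibility and acceptability are named as primary. The Objectives nevertheless list the variability and effect size of the outcomes, with fatigue singled out, as something the study must deliver.

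**The concern.** Poisson and negative binomial regression are models for event counts. A bounded rating or a questionnaire score has no natural link between its mean and its variance. Poisson imposes one: the variance must equal the mean. Its standard error is therefore fixed by where the scale's numbers sit. The same clinical spread gives a different interval on a 1-10 scale than on a scale centred at 55. Negative binomial relaxes this in one direction only, since it allows variance above the mean but not below.

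A second issue is conditional. All the named models, in their plain form, treat rows as independent, and the NRS gives many rows per person. That would matter only if ratings were entered row by row.

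At stake are the fatigue interval and p value. They bear on a listed objective and decide whether the joint model is run. The trial's primary conclusions on feasibility do not depend on them.

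**Working it through.** There is no stated figure to reproduce: the article gives no SD, within-person correlation (ICC), effect size or significance level for fatigue. A two-sided 5% level is implied by the 95% intervals. All means, SDs and ICCs below are assumptions, shown as ranges.

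**1. Poisson on one value per participant.** With equal arms and no true difference, the Poisson Wald statistic has true standard deviation of about √(variance/mean) instead of 1. The actual error of a nominal 5% test is therefore about 2[1 − Φ(1.96/√(variance/mean))].

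| Score (assumed) | Variance/mean | Actual error |
|---|---|---|
| One NRS rating, mean 5, SD 1.5 | 2.25/5 = 0.45 | 0.3% |
| One NRS rating, mean 5, SD 2 | 4/5 = 0.80 | 2.8% |
| Questionnaire total, mean 24, SD 6 | 36/24 = 1.50 | 11% |
| Questionnaire total, mean 24, SD 7 | 49/24 = 2.04 | 17% |
| T-type score, mean 55, SD 8 | 64/55 = 1.16 | 7% |
| T-type score, mean 55, SD 10 | 100/55 = 1.82 | 15% |

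Simulation with 20 per arm and no effect agrees. For ratings rounded and clipped to 1-10 with mean 5.5, Poisson error was 0.3%, 1.9% and 5.4% at SD 1.5, 2.0 and 2.5. The last value shows that Poisson can land near 5%, but only where the variance happens to be close to the mean. A Gaussian test on the same data gave 4.9% to 5.3%.

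**2. Negative binomial on one value per participant.** Simulated on the overdispersed scores (2,000 to 3,000 replicates), it gave 5.4% to 5.5% for the questionnaire total and 5.7% to 6.5% for the T-type score. It roughly holds its level there. For a single rating with variance/mean below 1 (0.45 to 0.80 above), it has no parameter value that fits.

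**3. The conditional clustering risk.** Complete NRS data give 3 × 7 × 6 = 126 ratings per person, or 40 × 126 = 5,040 in all. If these were entered as independent rows, the design effect would be 1 + (126 − 1) × ICC and the actual error 2[1 − Φ(1.96/√design effect)].

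| ICC | Design effect | Error by formula | Simulated Gaussian | Simulated Poisson |
|---|---|---|---|---|
| 0.1 | 13.5 | 59% | 60% | 53% |
| 0.3 | 38.5 | 75% | 75% | 70% |
| 0.5 | 63.5 | 81% | 80% | 77% |
| 0.7 | 88.5 | 84% | 82% | 79% |

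If two post-baseline Neuro-QOL values per person were treated as independent, the design effect would be 1.5 to 1.7 at ICC 0.5 to 0.7, giving 11% to 13%.

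**4. With one mean rating per participant.** A t test of 20 against 20 on the same simulated 126-rating data gave 4.4% to 5.5% for ICC 0.1 to 0.7, which is nominal. A mixed model with a participant effect addresses the same clustering but was not simulated.

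**The case against.** The strongest reply is that the article commits to very little. The starting model has no named family, so it may be Gaussian, and a Gaussian model on one value per participant holds its level. The count regressions are only examples of what may be done if fit is poor. The sentence speaks of data in general and follows one that also mentions physical functioning, so it need not be aimed at fatigue alone. Negative binomial, the first example named, handles the overdispersed scores where Poisson does worst. The fatigue comparison is not primary, and the variability estimate for the next trial can be a descriptive SD that needs no Poisson standard error.

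Most of this stands, and it limits the point. A reader might infer that the fatigue p values and intervals will be wrong because 126 repeated ratings go into an independence model. The documents do not support that. Nothing says the ratings are pooled as rows, and the choice of measure, unit of analysis and handling of repeated measures are details an article commonly leaves to the full protocol or analysis plan. A reader might also infer that both count models always inflate error. They do not: Poisson on a single rating is mostly conservative, and negative binomial is close to nominal for overdispersed scores.

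What the reply does not remove is that the article itself names Poisson in the paragraph on the fatigue comparison, and none of the fatigue measures is a count. An unseen plan may supply missing detail, but this option would still be unsuited to the scores.

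**Conclusion.** The point holds in a limited form. Poisson regression is a stated but optional route for the fatigue comparison, and if taken it would give error bars set by the scale's numbering. On one value per participant, a nominal 5% test would run at about 0.3% to 3% for a single 1-10 rating (mean 5, SD 1.5 to 2) and about 7% to 17% for questionnaire-type scores (mean 24, SD 6 to 7; mean 55, SD 8 to 10). Negative binomial is unsuitable where the variance is below the mean and acceptable in level where it is above.

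The 50% to 85% figures (ICC 0.1 to 0.7) describe what independent-row analysis of all NRS ratings would do, not what the article says will be done. All sizes rest on assumed means, SDs and correlations. The matter is secondary to feasibility, but worth correcting because it bears on a listed objective and on the trigger for the joint model.

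**What to change.** In Statistical methods, Acceptability, remove Poisson as an option for the fatigue scores, and remove negative binomial for the 1-10 rating. State instead a linear model on the original score, with robust or bootstrap intervals if residuals are skewed.

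- **NRS:** use one mean per participant over a stated period, or all ratings in a linear mixed model with a participant random effect. Ratings begin only after the first drink, so there is no pre-treatment NRS value to adjust for.
- **Neuro-QOL:** use the week 6 score adjusted for its baseline value.

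The cost is analysis wording only, with no new data or visits. Intervals will be wider than those from any model that treats repeated ratings as independent.
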